### 2. Trial registration

**2a.** ID ClinicalTrials.govNCT05538520

#### 2b. Administrative Information

|                               |                                                                                                                                                                                                           |
|-------------------------------|-----------------------------------------------------------------------------------------------------------------------------------------------------------------------------------------------------------|
| Other Study ID Numbers        | Pilates_stretching                                                                                                                                                                                        |
| Has Data Monitoring Committee | No                                                                                                                                                                                                        |
| U.S. FDA-regulated Product    | Studies a U.S. FDA-regulated Drug Product: No
Studies a U.S. FDA-regulated Device Product: No                                                                                                          |
| IPD Sharing Statement         | Plan to Share IPD: No
Plan Description: Data regarding the study will be shared in the publication linked to this record, as a main part of the manuscript and supplementary documents when necessary. |
| Current Responsible Party     | [name], Universidade Estadual do Norte do Parana                                                                                                                                   |
| Current Study Sponsor         | Universidade Estadual do Norte do Parana                                                                                                                                                                  |
| PRS Account                   | Universidade Estadual do Norte do Parana                                                                                                                                                                  |

### 3. Protocol version

1st version on 8/3/2023

### 4. Funding

This study was financed in part by the Coordenação de Aperfeiçoamento de Pessoal de Nível Superior – Brazil (CAPES) – Finance Code 001.

## **INTRODUCTION**

### **6a. Background and rationale**

Stretching exercises are widely used in training routines, typically preceding or following main exercise practice, whether the objective is related to rehabilitation [1] or physical conditioning [2], also aiming at improving performance in subsequent exercises involving musculoskeletal fitness [3]. In addition, stretching is considered the main exercise to gain flexibility [4], although resistance training alone can promote increased flexibility [5]. However, the performance of stretching exercises, preceding muscle strengthening exercises, has been questioned in the literature over the last few years [6–8], which evidently can generate doubts in the definition of intervention protocols for the most diverse objectives.

For example, even considering that static stretching or techniques such as proprioceptive neuromuscular facilitation are effective for improving flexibility, studies show that performing these forms of stretching, preceding muscle strengthening training, can generate a significantly lower gain in strength, power and muscular resistance when compared to its nonperformance [9–11]. On the other hand, the literature has noted that dynamic stretching does not seem to impair the subsequent development of these components of musculoskeletal fitness and may, in some cases, enhance its gain [12, 13]. However, most studies within this theme involve acute interventions, which may not reflect long-term effects [14]. Furthermore, some forms of stretching have not been investigated, such as the stretching exercises used in the practice of Pilates, which despite having a dynamic characteristic, are performed at a slow pace, following principles such as concentration, breathing, control, precision, centralization and fluidity [15].

It is common in Pilates protocols for stretching exercises to be performed at the beginning of the session, preceding muscle strengthening exercises [16–18]. However, how this impacts a possible harm or benefit in the development of variables such as strength, power and muscular endurance is unknown. Pilates is a technique used both in cases of rehabilitation and for physical conditioning, involving stretching exercises and muscle strengthening [15, 19]. The popularity of the technique has increased; however, scientific research is still in its infancy. In the USA, for example, between 2010 and 2021, an

average of 10 million Pilates practitioners were registered per year [20]. In Brazil, when grouped alongside yoga, gymnastics and stretching, it is characterized as the sixth most practiced physical activity [21].

Understanding the impact of stretching exercises used in Pilates on components of musculoskeletal fitness can help physical exercise professionals define intervention protocols, whether aimed at rehabilitation or physical conditioning.

**6b.** In order to be able to detect the influence of Pilates exercise stretching on musculoskeletal fitness components, it is necessary to adopt as a comparator a group that performs the same activities as the experimental group, however, without the addition of stretching exercises.

## **7. Objectives**

To verify the effects of Pilates stretching exercises performed at the beginning of sessions on flexibility, strength, power and muscular endurance.

## **8. Trial design**

Randomized and controlled clinical trial.

## **METHODS: PARTICIPANTS, INTERVENTIONS, AND OUTCOMES**

### **9. Study setting:**

Center for Health Sciences at the Universidade Estadual do Norte do Paraná, Brazil.

### **10. Eligibility criteria:**

#### **Inclusion Criteria**

- ages between 18 and 45 years
- normoweights (body mass index between 18.5 to 24.9 kg/m^2)
- not be participating in physical exercise programs for at least six months
- be healthy, according to the Physical Activity Readiness Questionnaire
- not report any medical restrictions for physical exercise
- no history of injury, trauma or illness within the last six months
- not having undergone previous surgery in the last six months
- not have musculoskeletal, cardiorespiratory and neurological disorders that prevent the performance of assessment and intervention protocols
- not be under the action of medications that cause muscle relaxation or that can inhibit muscle tonic action
- not use food supplements or anabolic steroids

- not being on a calorie-restricted diet

#### Exclusion Criteria

- start practicing another type of physical exercise during the study period
- not being able to perform the pre-intervention assessment or the intervention exercise protocol
- emergence of lesions that do not allow the continuity of interventions
- withdraw from participating in the study

### 11. Interventions

**11a.** Intervention 1 – Traditional Pilates: This group will perform a traditional Pilates session, which consists of stretching exercises, followed by exercises to strengthen the core (trunk flexors and extensors), lower limbs and upper limbs. The total duration of the intervention in this group should be approximately 50 minutes.

Intervention 2 – Pilates without stretching: This group will conduct a non-traditional Pilates session. This is because stretching exercises will be excluded. The muscle strengthening exercises will be the same as in the TP group, so that it is possible to discuss the influence of the inclusion/exclusion of stretching for the considered outcomes. The total duration of the intervention in this group should be approximately 35 minutes.

**11b.** a participant must discontinue the intervention when at his own request (personal reasons), or due to any health problem that makes its continuity unfeasible (eg appearance of injury).

**11c.** adherence monitoring will occur through an attendance/absence form.

**11d.** all participants will be instructed to maintain their usual routine, especially with regard to physical activity and eating habits.

### 12. Outcomes

- Change in muscle strength of knee extensors and flexors [Time Frame: Pre (baseline) and post-intervention assessment (after 8-weeks)]. Assessment of muscle strength with elastic resistance
- Change in strength/endurance by 1-minute sit-up test [Time Frame: Pre (baseline) and post-intervention assessment (after 8-weeks)]. Assessment of abdominal muscle strength/endurance in 1-minute
- Change in muscle strength by handgrip test using hand dynamometer [Time Frame: Pre (baseline) and post-intervention assessment (after 8-weeks)]. Assessment of handgrip muscle strength
- Change in the muscular resistance of the trunk extensors by the Sorensen test [Time Frame: Pre (baseline) and post-intervention assessment (after 8-weeks)]. Assessment of the muscular resistance of the trunk extensors (Sorensen)

- Lower limb muscle power [Time Frame: Pre (baseline) and post-intervention assessment (after 8-weeks)]. Assessment of lower limb muscle power by vertical jump
- Flexibility [Time Frame: Pre (baseline) and post-intervention assessment (after 8-weeks)]. Flexibility assessment by the sit-and-reach test
- Affective valence [Time Frame: The scale will be applied at the end of each exercise session, over the 8 weeks, 3x a week, thus totaling 24 assessments throughout the study.]. Assessment of affective valence by the Feeling Scale. It ranges from +5 (very good) to -5 (very bad). Positive values represent pleasure, while negative values represent displeasure.

### **13. Participant timeline**

Registration will remain open until the sample size is reached. Next, a week will be reserved for the initial assessments (pre-intervention), followed by eight weeks of intervention. Finally, in the following week, the final evaluations (post-intervention) will be carried out.

### **14. Sample size**

The sample calculation was performed using the Bioestat 5.3 program (Instituto Mamirauá, Amazonas, Brazil), taking into account the muscle strength values of the lower limbs available in a previous study [22]. In this case, the postintervention mean and standard deviation for muscle strength of the lower limb evaluated by the 10-RM test (kg) in the Leg Press between the group "dynamic stretching combined with resistance training" ( $337.1 \pm 37.29$ ) vs the group "resistance training alone" ( $374.3 \pm 32.07$ ) was used, with test power at 80% and alpha value at 0.05, which generated the need for at least 16 participants in each group, already considering an additional 15%, to avoid a decrease in statistical power in case of sample loss.

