## **METHODS: ASSIGNMENT OF INTERVENTIONS (FOR CONTROLLED TRIALS)**

### **16. Allocation**

**16a.** Sequence generation: The randomization process will be carried out by a blinded researcher who is not part of the study team. Random numbers will be generated by online software (randomization.com), which will distribute participants into two groups of equal size (1:1).

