## **20. Statistical methods**

**20a.** Aiming at greater robustness and precision in data analysis, analysis of co-variance (ANCOVA) is planned, with baseline data used as co-variables, so that, strictly speaking, the effective differences between the groups in the post-intervention period are compared.

**20b.** In order to demonstrate the effects of the intervention considering only the subjects who completed the protocol, an analysis per protocol is also foreseen, even if in a secondary way.

**20c.** For the main analyses, performed on an intention-to-treat basis, imputations are anticipated for participants who do not complete interventions. In this case, data from the initial assessment (pre-intervention) will be replicated in the final assessment (post-intervention).

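### Section 14's 15% margin does not preserve 80% power after 15% loss on a two-sided t-test, and it takes no account of the baseline carry-forward in 20c

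*Protocol*

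**What the plan says.** Protocol Section 14 takes post-intervention leg-press 10-RM from a previous study: 337.1 kg (SD 37.29) with dynamic stretching plus resistance training, and 374.3 kg (SD 32.07) with resistance training alone. The calculation was run "with test power at 80% and alpha value at 0.05". Its result is reported together with the allowance for losses: "which generated the need for at least 16 participants in each group, already considering an additional 15" per cent. The purpose of the margin is stated: "to avoid a decrease in statistical power in case of sample loss". The section gives neither the sidedness of the test nor the formula used for the inflation.

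Section 16a allocates 1:1. In Section 20a, "analysis of co-variance (ANCOVA) is planned, with baseline data used as co-variables". Section 20c sets the rule for non-completers in the main, intention-to-treat analysis: "data from the initial assessment (pre-intervention) will be replicated in the final assessment (post-intervention"). Section 20b makes the analysis of completers secondary.

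**The concern.** Section 14 claims a specific property: 16 per group holds the target power if about 15% are lost. There are two reasons to doubt it.

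- At about 14 per group the large-sample formula is slightly optimistic, and multiplying by 1.15 does not offset a 15% loss, because 1.15 x 0.85 = 0.98.
- The margin assumes that lost participants leave the analysis and n falls. Under 20c they stay in, with a post-intervention value that carries no treatment effect. Nothing in Section 14 allows for that dilution.

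If the claim stands unqualified, a null result will be read against an 80% figure that was not derived for the analysis reported.

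**Working it through.** **Inputs (Section 14).** Difference = 374.3 - 337.1 = 37.2 kg. Pooled SD = sqrt((37.29² + 32.07²)/2) = 34.78 kg. d = 37.2/34.78 = 1.07. Power 80%, alpha 0.05, allocation 1:1 (Section 16a). Two-sided testing is assumed, because Section 6a asks about possible harm or benefit.

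**1. Reproducing the 16.** Normal approximation: n = 2(1.960 + 0.842)²/d² = 13.72 per group. Then 13.72 x 1.15 = 15.78, which rounds up to 16. The match suggests this route; the protocol does not state it.

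**2. Power if losses leave the analysis.** The t-test column uses the noncentral t with df = 2n - 2 and noncentrality d x sqrt(n/2).

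| Per group | Two-sided t | Normal approximation |
|---|---|---|
| 16 (no loss) | 83.3% | 85.7% |
| 15 | 80.7% | 83.4% |
| 14 | 77.8% | 80.8% |
| 13.6 (= 16 x 0.85) | 76.5% | 79.7% |
| 13 | 74.4% | 77.8% |

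The t-test needs 15 evaluable per group. Allowing for 15% loss, 15/0.85 = 17.6, so 18. By the normal approximation with division, 13.72/0.85 = 16.14, so 17. The gap is 1 to 2 participants per group.

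**3. Power if losses are carried forward (20c), unadjusted.** All 16 per group are analysed. Randomised groups share the same expected baseline, so copied values contribute no group difference. With 15% copied in each group the expected difference is 0.85 x 37.2 = 31.6 kg. Power at n = 16 is then 70.1% (t) or 73.0% (normal). Simulation also captures the extra spread from mixing baseline and post-intervention values. It gives 67 to 69% when the common baseline is assumed to lie 18.6 to 37.2 kg (0.5 to 1.1 SD) below the higher post-intervention mean, and about 62% at 60 kg (1.7 SD) below.

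**4. Power for the planned main analysis: ANCOVA with carry-forward.** Simulation with 16 per group, 15% carried forward at random, and equal SDs at both times. The correlation and the baseline gap are assumptions, because the protocol gives neither.

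| Pre-post correlation | Gap 0.5 to 1.1 SD | Gap 1.7 SD |
|---|---|---|
| 0.3 | 73 to 75% | 66% |
| 0.5 | 81 to 84% | 73% |
| 0.7 | 93 to 95% | 84% |

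By the simple dilution formula, which ignores the gap, ANCOVA reaches 80% at a correlation of about 0.46.

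**The case against.** The strongest reply is that nothing was miscalculated. The 16 follows exactly from the stated inputs by a common formula and a literal reading of an additional 15%. By that formula power after loss is 79.7%, or 80.8% if two of 16 are lost, which is on target for practical purposes. This stands: 16 is not an arithmetic error, and the shortfall in step 2 is small and depends on the method.

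It can also be said that sidedness is unstated, and that a one-sided t-test would have 85.7% power at 13.6 per group. That carries less weight. The research question runs in both directions, and a one-sided calculation gives 13 to 15 per group after inflation, not 16.

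A reader might infer that the two losses add up, with fewer participants and then dilution on top. They do not. For a given participant either n falls or a baseline value is copied, and under 20c all 16 are analysed.

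Finally, the unadjusted figures do not describe the planned analysis. ANCOVA usually gains power, and sizing a trial without the covariate is normally conservative. This also stands, and it limits the conclusion. Taking the effect from a leg-press measure is openly disclosed and is not a fault in itself, but it should be labelled as an assumption for the knee-strength outcome.

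**Conclusion.** The point holds in a limited form. On the protocol's own inputs and a two-sided t-test, the 15% margin does not keep 80% power after a 15% loss: it leaves 74 to 78%, about 1 to 2 participants per group short. The margin also addresses the wrong mechanism, because 20c turns losses into dilution, with about 67 to 70% power unadjusted for moderate baseline gaps and less for larger ones.

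A reader might go further and conclude that the trial is underpowered for its main analysis. The documents do not support that. With ANCOVA and carry-forward, power passes 80% at a correlation of 0.5 if the baseline gap is moderate, and falls short at 0.3 or with a large gap. The protocol gives no value for either quantity, so neither a shortfall nor the 80% is established. What can be said is that the stated protection was not derived for the analysis that will be run. This calls for correcting a stated property, not for resizing the trial.

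**What to change.** Keep 16 per group and restate Section 14, for example:

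> Two-sided alpha 0.05; d = 1.07 is borrowed from leg-press 10-RM and assumed for knee strength. Sixteen per group gives 83% power with no loss, and 74 to 78% if 15% are lost and excluded (unadjusted comparison). Under the main analysis (ANCOVA with baseline carried forward for 15%), power is about 73 to 75% at a pre-post correlation of 0.3, 81 to 84% at 0.5 and 93 to 95% at 0.7, assuming baseline 0.5 to 1.1 SD below the higher post-intervention mean. It is lower for a larger gap (about 73% at a correlation of 0.5 for a gap of 1.7 SD).

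Name the sample-size and inflation formulas used, and say which correlation and baseline gap the investigators consider plausible and why. Remove the unqualified statement that the 15% margin avoids a decrease in power. The power figure should be attached to the analysis with carry-forward, since the completers' analysis is secondary.

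The cost is one rewritten paragraph and a slightly less favourable stated figure, with no extra participants.

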### **15. Recruitment**

Recruitment should occur mainly through disclosure on social media (internet).

## **METHODS: ASSIGNMENT OF INTERVENTIONS (FOR CONTROLLED TRIALS)**

### **16. Allocation**

**16a.** Sequence generation: The randomization process will be carried out by a blinded researcher who is not part of the study team. Random numbers will be generated by online software (randomization.com), which will distribute participants into two groups of equal size (1:1).

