## **METHODS: DATA COLLECTION, MANAGEMENT, AND ANALYSIS**

### **18. Data collection methods**

**18a.** Data collection will be carried out by an experienced evaluator, a professional with a degree in Physiotherapy and Physical Education. The tests performed and their measurement properties are described below:

*Muscle strength of the knee extensors and flexors* – It will be evaluated using elastic bands (Thera Band GmbH, Hadamar, Germany) as previously described [23]. Participants will be tested on their dominant side. After a 10-minute warm-up on a cycle ergometer (60 rpm, 80 W), participants will be positioned on the seat of a standardized chair. Participants will be asked to perform the maximum number of repetitions with an elastic band of intermediate resistance (black color). If they managed to perform 11 repetitions, an elastic band of greater resistance will be selected for the next attempt. This procedure will be repeated (maximum of 5 attempts with 5 minutes of rest between attempts) until the participant is able to perform 10 or fewer repetitions. The following prediction equation will be used:  $1\text{-RM} = \text{resistance in kg} / (1.0278 - [0.0278 \times \text{reps}])$  [24]. This test demonstrated high validity against concentric peak torque measured by an isokinetic dynamometer ( $r = 0.93$ ) and test-retest reliability ( $\text{ICC} \geq 0.98$ ,  $\text{CV}[\%] \leq 3.44$ ) [23].

*Vertical jump* – The countermovement jump test (sargent jump) will be used as an indicator of lower limb muscle power. The objective of the test will be to verify the highest height at the peak of the vertical jump, measuring two points marked on the wall by the participant himself, with the fingers of one of the chalk-stained hands: (1) the initial measurement will be obtained with the participant standing and erect, keeping the dominant arm extended parallel and above the head, marking the wall with chalk as high

as possible, keeping the soles of the feet completely in contact with the ground; (2) the second measurement will be obtained with the participant touching the wall with the fingers of the hand as high as possible during the peak of the vertical jump. Three attempts will be allowed with a two-minute interval between them, with the highest value in centimeters being recorded among the three attempts. This test demonstrated high validity ( $r = 0.99$ ) and test-retest reliability ( $r = 0.99$ ) [25].

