*Handgrip strength* – To determine handgrip strength, a digital hydraulic dynamometer (Saehan SH1001) will be used. The participant must be seated, with the spine erect and the knees flexed at  $90^\circ$ . The dominant upper limb tested will be positioned with the shoulder in adduction and neutral rotation, wrist in neutral position and elbow at a  $90^\circ$  angle. Participants will be instructed to perform three repetitions of maximum contraction maintained for five seconds, with a 60-second interval between each repetition. The maximum voluntary contraction will be determined by the highest value obtained in the three attempts. This instrument demonstrated excellent validity ( $r \geq 0.97$ ) and test-retest reliability ( $r \geq 0.98$ ) [26].

*Abdominal muscle endurance* – To assess abdominal muscle endurance, the 1-minute sit-up test will be performed. In dorsal decubitus, the participant should flex the knees, keeping the soles of the feet in contact with the ground, with the feet apart at a distance identical to the width of the hips. Her arms should be crossed over her chest. The evaluator will place his hands on the participant's feet to keep them in permanent contact with the ground. At the signal emitted by the evaluator, the participant will raise the torso until the anterior face of the forearms comes into contact with the thighs, immediately returning to the initial position, with contact of at least the anterior half of the scapulae on the ground. These movements should be repeated over one minute. The objective of the test will be to try to perform as many executions as possible in the stipulated time. This test demonstrated high test-retest reliability ( $ICC = 0.91$ ) [27].

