### **26. Consent or assent**

**26a.** The principal investigator will obtain informed consent from each participant. For this, he should explain in clear language all aspects of the study, such as: evaluation measures, intervention procedures, risks and benefits. In addition, a Consent Term approved by the Ethics Committee that approved the study must be read by the participant, who must sign the document if he/she wishes to participate in the study.

**26b.** If it is necessary to use the image of a person demonstrating the exercises of the intervention protocol, an informed consent will also be required specifically for this purpose.

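### Both sexes are eligible, but neither the randomisation nor the ANCOVA takes account of sex, which costs precision and leaves avoidable imbalance in a trial of about 32 people

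*Protocol*

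**What the plan says.** The inclusion criteria in section 10 cover age ("ages between 18 and 45 years"), body mass index, activity and health. None concerns sex.

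The wording elsewhere does not settle the matter. Section 26a describes a participant "who must sign the document if he/she wishes to participate in the study". In section 18a the jump test is written for a man ("measuring two points marked on the wall by the participant himself") and the sit-up test for a woman ("Her arms should be crossed over her chest").

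Section 16a describes a generator "which will distribute participants into two groups of equal size (1:1" and names no stratification factor. Section 14 asks for at least 16 per group, so about 32 in total.

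The physical outcomes in section 18a are absolute: predicted 1-RM in kg, jump height in cm, highest handgrip value, sit-up count, Sorensen holding time and reach distance. None is scaled to sex or body size. Section 20a plans ANCOVA with "baseline data used as co-variables". Affective valence (sections 12 and 18a) is collected only at the end of exercise sessions.

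**The concern.** As written, the trial may enrol a mixed group. If the outcomes differ by sex, two things follow from leaving sex out of both the allocation and the model.

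First, arms of 16 can differ noticeably in sex composition by chance. Baseline adjustment corrects most of this, but not all of it.

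Second, a single pre-post slope fitted to a mixed sample is pulled up by the gap between the sexes. It is then steeper than the slope within either sex, so the adjustment is less efficient than it could be.

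Affective valence is a separate case: with no pre-intervention value, any sex difference in it passes straight through whatever imbalance occurs.

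Eligibility and the allocation list have to be settled in the protocol. A later analysis plan can add a covariate, but cannot change who was enrolled or how they were allocated.

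**Working it through.** **The plan's own figure.** Section 14 gives 337.1 ± 37.29 and 374.3 ± 32.07, "with test power at 80% and alpha value at 0.05". The difference is 37.2 and the pooled SD is √((37.29² + 32.07²)/2) = 34.78. Two-sided, n = 2 × ((1.960 + 0.842) × 34.78/37.2)² = 13.7 per group, and 13.7 × 1.15 = 15.8, so 16. The stated figure reproduces.

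**Assumptions.** The protocol gives none of these: 16 men and 16 women; female:male mean ratio f of 0.6 or 0.7; within-sex CV of 10%; within-sex pre-post correlation ρ of 0.5, 0.7 or 0.85.

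**Chance imbalance.** With 16 women among 32 people and 16 drawn to one arm (hypergeometric), the split is 10 v 6 or worse with probability 0.289, and 11 v 5 or worse with probability 0.076.

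**Variance components.** Set the male mean to 1. The between-sex variance is B = (1 − f)²/4 and the average within-sex variance is W = (0.10² + (0.10f)²)/2.
- f = 0.6: B = 0.0400, W = 0.0068, overall mean 0.80, total CV √0.0468/0.80 = 27%.
- f = 0.7: B = 0.0225, W = 0.00745, overall mean 0.85, total CV √0.02995/0.85 = 20%.

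**Planned model against a model with sex.** With equal spread before and after, the pooled correlation is r = (B + ρW)/(B + W), which is also the pooled slope. The residual variance is W(1 − ρ)(1 + r) under the planned ANCOVA and W(1 − ρ)(1 + ρ) with a sex term. The ratio is (1 + ρ)/(1 + r).

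| ρ | r (f = 0.6 / 0.7) | Variance cut, formula | Variance cut, simulation (strata + sex term) | Power as planned | Power with strata + sex term |
|---|---|---|---|---|---|
| 0.5 | 0.927 / 0.876 | 22% / 20% | 19–25% | 0.57–0.58 | 0.69 |
| 0.7 | 0.956 / 0.925 | 13% / 12% | about 15% | 0.78–0.79 | 0.84 |
| 0.85 | 0.978 / 0.963 | 6.5% / 5.7% | 5–10% | 0.97 | hardly changes |

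Power is from simulation, at 16 per arm and an effect of 8% of the mean. The formula covers only the sex term. The simulation also includes the balance gained by stratifying and carries some sampling error.

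**Where the gain comes from.** At ρ = 0.5, simulated power goes from 0.58 (planned) to 0.66–0.68 with a sex term alone and 0.68–0.69 with strata as well. At ρ = 0.7 it goes from 0.78–0.79 to 0.81–0.83 and then to 0.84–0.85. Stratification itself adds about 1 to 4 points.

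**Shift left by a 10 v 6 split.** The share of women differs by 4/16 = 0.25. Unadjusted, the group difference moves by 0.25 × 0.4/0.80 = 12.5% of the mean (f = 0.6) or 0.25 × 0.3/0.85 = 8.8% (f = 0.7). The planned ANCOVA leaves a fraction 1 − r of that:
- ρ = 0.5: 12.5 × 0.073 = 0.9% and 8.8 × 0.124 = 1.1%.
- ρ = 0.7: 12.5 × 0.044 = 0.5% and 8.8 × 0.075 = 0.7%.

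The planning difference is 37.2/374.3 = 9.9% to 37.2/337.1 = 11.0% of the mean.

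**The case against.** Unstratified 1:1 randomisation by an outside researcher, with sealed opaque envelopes, is legitimate. Under these same assumptions the planned ANCOVA rejected a true null in 4.3–5.5% of simulated trials, so validity is intact. That stands.

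The 8% effect is also smaller than the protocol's own. At about 10.4%, the planned unstratified ANCOVA has power 0.77–0.82 at ρ = 0.5, 0.94–0.95 at 0.7 and above 0.99 at 0.85, so the intended 80% is broadly kept. That also stands, and it limits the weight of the point.

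A covariate may be left to an analysis plan that is not shown here, and the baseline data in 20a could be read to include sex. The context, post-intervention comparison adjusted for the pre-intervention state, points to each outcome's baseline value. If sex is meant, 20a should name it. Eligibility and allocation are not matters for an analysis plan.

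Two stronger readings are tempting and should not be drawn:
- **That sex imbalance would confound the outcomes, all in one direction.** An imbalance of 10 v 6 or worse is absent in 71% of allocations, the adjustment removes most of its effect when it occurs, and the documents give no direction of any sex difference.
- **That the planning groups were far more homogeneous because of sex.** Their CVs are 37.29/337.1 = 11.1% and 32.07/374.3 = 8.6%, but they come from a different test (10-RM leg press), and the protocol states the sex mix of neither sample.

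The mixed pronouns are probably loose generic wording. They show only that the text does not settle the question.

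**Conclusion.** The point holds as one of efficiency and clarity. The protocol leaves both sexes eligible and uses sex in neither the allocation nor the stated model. The result would not be invalid.

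The loss is worth recovering if pre-post correlation within sex is moderate (about a fifth to a quarter of the variance at 0.5) and small if it is high (5–10% at 0.85). These sizes rest wholly on the assumed even sex mix, ratio of 0.6–0.7 and within-sex CV of 10%. They shrink if the sex gap is smaller or the mix lopsided, and vanish if only one sex is enrolled.

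Affective valence is the one outcome without a baseline safeguard. It is exposed only if it differs by sex, on which the protocol is silent.

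**What to change.** State in section 10 whether both sexes are eligible.

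- **If both are:** in 16a, generate separate blocked 1:1 lists for men and women, with the envelopes labelled by stratum. In 20a, add sex as a fixed factor beside the baseline value, and include it in the comparison of affective valence too.
- **If only one is intended:** make that an inclusion criterion. No stratification is then needed.

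The cost is a second list from the same generator and one residual degree of freedom (28 instead of 29 with 32 participants). No further participants, visits or staff are needed. Section 13 keeps registration open until the sample size is reached and only then starts the assessments, so the sex of every participant can be known before the intervention begins. If the allocation list has already been used, the sex term alone still recovers most of the gain.
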